**Methods:**

This study proposes to measure blood C-reactive protein (CRP) levels before the initiation of treatment in 200 participants with MDD. Study participants are then assigned into one of two study strata: either into the ‘Depression with inflammation’ stratum (CRP levels > 3 mg/L); or into the ‘Depression without inflammation’ stratum (CRP levels ≤ 3 mg/L). Within each of the two study strata, participants randomly receive either antidepressant medication alone (vortioxetine) plus anti-inflammatory medication (celecoxib) or vortioxetine plus placebo for six weeks. At the end of the treatment period, participants have the opportunity to continue vortioxetine alone for a six-month post-trial period. Clinical outcomes are measured at baseline, fortnightly during the treatment period and at the three-month and six-month post-trial visits. The primary outcome is change in MADRS score, with a primary endpoint of a score reduction by 50% from baseline to six weeks (end of augmentation treatment with celecoxib). Secondary clinical outcomes are changes in the cognitive dimensions of depression (cognitive function, emotion processing and social cognition). Biological outcome measures (levels of CRP and other inflammatory markers) are measured at baseline, after six weeks of treatment and at the six-month post-trial visit.

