## Methods and design

### Objectives

The primary objective of this study is to investigate the antidepressant efficacy, measured by Montgomery–Åsberg Depression Rating Scale (MADRS) score, of the six-week combined treatment of MDD with antidepressant medication (vortioxetine) plus anti-inflammatory medication (celecoxib). We hypothesise that a higher efficacy and larger reduction in symptoms of depression will be observed after six weeks when treatment is combined (antidepressant and anti-inflammatory) compared to the treatment with antidepressant alone, in individuals with baseline inflammation (i.e. with baseline CRP levels > 3 mg/L). In addition, we hypothesise that no difference between treatments will be observed in individuals with no baseline inflammation (i.e. with baseline CRP levels < 3 mg/L) (see Table 1).

**Table 1 Tab1:** Objectives and hypotheses of the study. Table stating study objectives and hypothesis in a generic way and in a drug-specific way

	Generic way	Drug-specific way
Primary objective	To investigate the antidepressant efficacy of the 6-week combined treatment of MDD with antidepressant plus anti-inflammatory	To investigate the antidepressant efficacy of the 6-week combined treatment of MDD with vortioxetine plus celecoxib 400 mg
Primary hypothesis	A higher efficacy and larger reduction in symptoms of depression will be observed after 6 weeks when treatment is combined (antidepressant and anti-inflammatory) in individuals with baseline inflammation	A higher efficacy and larger reduction in symptoms of depression will be observed after 6 weeks when treatment is combined (vortioxetine and celecoxib 400 mg) in individuals with baseline inflammation
Secondary objective 1	To investigate the anti-inflammatory effects of a combined treatment of MDD with antidepressant and anti-inflammatory in individuals with baseline inflammation (CRP levels > 3 mg/L) over a 6-week period	To investigate the anti-inflammatory effects of a combined treatment of MDD with vortioxetine and celecoxib 400 mg in individuals with baseline inflammation (CRP levels > 3 mg/L) over a 6-week period

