### Recruitment and study design

A total of 200 patients with MDD will be included in the study. Recruitment and treatment take place in the wider Central Adelaide Local Health Network (CALHN), with all participant appointments being held in the Clinical Research Facility in the Health and Medical Sciences Building, Discipline of Psychiatry, University of Adelaide. In addition to this, and to ensure that required numbers of study participants are recruited, people from the general population who meet the inclusion criteria are able to engage with the proposed study, as it is made available through advertisement. Participants are free to withdraw from the study at any time.

The study is designed as a parallel group RCT with a superiority framework, investigating 200 participants with MDD over six weeks in the primary phase followed by a six-month post-RCT follow-up period (Fig. 1). The study proposes to measure the inflammatory marker CRP before the commencement of treatment. Following CRP measurement, study participants are then assigned into one of two study strata based on CRP levels. The first of these study strata is made up of 100 individuals with CRP levels > 3 mg/L (the ‘Depression with inflammation’ stratum) and the second study stratum is an active control, made up of 100 individuals with CRP levels ≤ 3 mg/L (the ‘Depression without inflammation’ stratum). In each stratum, participants are randomly allocated in a 1:1 ratio to augmentation of vortioxetine antidepressant treatment with either celecoxib or placebo. Following six weeks of concomitant administration of celecoxib or placebo with vortioxetine, the celecoxib or placebo is then stopped and the participants are treated with vortioxetine only for an additional two weeks. This allows the opportunity to assess the efficacy of taking vortioxetine alone. While the primary time point is the six weeks in which we compare vortioxetine with augmentation against vortioxetine without augmentation, following the RCT phase, all participants have the opportunity to continue on vortioxetine without celecoxib or placebo for another six months during a post-RCT observational study period.

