## Results analysis

The primary outcome (change in MADRS score from baseline to week 6) will be analysed using a mixed effects model for repeated measurements (MMRM, all available data), with freely varying mean and covariance structures. Treatment will be included as fixed factors. The baseline CRP level and stratified group (‘Depression with inflammation’ versus ‘Depression without inflammation’) will be controlled for. The existence of an interaction between inflammation at baseline and treatment will be assessed, recognising that the study is only powered to detect very large interaction effects. As previously recommended, ANCOVA will be used to account for possible baseline imbalance between treatment arms, thus allowing for participant differences [61]. As previously stated, we hypothesise that a reduction in MADRS score will be higher in participants receiving vortioxetine plus celecoxib in the ‘Depression with inflammation’ stratum compared to participants receiving the same treatment in the ‘Depression with no inflammation’ stratum. The potential treatment effect on CRP will be separated into the stratified strata (‘Depression with inflammation’ versus ‘Depression without inflammation’) as well as for the total group (all four groups). For dichotomous endpoints, such as response and remission, logistic regression with treatment as a factor and the baseline score as a covariate will be used. For continuous endpoints, the same methodology as that described for the primary endpoint will also be used. Continuous endpoints will also be analysed using observed case (OC) and last observation carried forward (LOCF), with LOCF being used to account for missing data and to perform sensitivity analysis. Association between function (FAST, Work Limitations Questionnaire and Sheehan Disability Scale) and endpoints addressing cognitive dysfunction will be explored by means of a partial correlation coefficient. Adverse events and the CSSR-S will be summarised using descriptive statistics.

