The primary outcome of this study will be MADRS score. It is expected that antidepressant combined with anti-inflammatory medication will reduce MADRS score by 50% from baseline to six weeks (end of treatment) in the ‘Depression with inflammation’ stratum of the study. We also expect that the reduction in MADRS score in the ‘Depression with inflammation’ stratum will be larger among those for whom vortioxetine treatment has been augmented with celecoxib than those in the same stratum receiving vortioxetine and placebo. Furthermore, the MADRS score reduction in the former group will also surpass that achieved by both treatment groups in the ‘Depression with no inflammation’ stratum. CRP level as a secondary outcome measure is expected to be reduced by 50% between baseline and six weeks in the group treated with antidepressant and anti-inflammatory medication in the ‘Depression with inflammation’ stratum of the study and is not expected to change in the group treated with antidepressant only in the same stratum. Similarly, CRP levels are not expected to be changed following both treatments in the ‘Depression with no inflammation’ stratum. Secondary outcome measures also include other inflammatory markers (TNF-α, IL-6 and IL-1β), levels which are expected to be reduced by 50%. In addition, a 50% improvement in cognitive dysfunction, functional measures and workplace functioning is expected. Finally, this study also assesses the safety of the anti-inflammatory celecoxib 400 mg when combined with vortioxetine by measuring potential side effects at each visit.

It is hypothesised that primary and secondary outcome measures will not show a statistically significant difference between participants receiving vortioxetine only and participants receiving vortioxetine plus celecoxib within the ‘Depression with no inflammation’ stratum of the study.

In summary, we anticipate that the results of this trial will allow the development of a decision aid for depression medication, thus improving treatment response and remission, especially in patients suffering from recurrent treatment resistant depression.

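### The logistic model stated for response and remission omits the CRP stratum and the treatment-by-stratum term, so it cannot give the within-stratum effect that the hypothesis concerns

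*Protocol article*

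**What the plan says.** All references are to the protocol article.

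- **Results analysis, dichotomous endpoints.** "For dichotomous endpoints, such as response and remission", the plan is that "logistic regression with treatment as a factor and the baseline score as a covariate will be used". No other term is listed, and no analysis population is named.
- **Results analysis, MADRS change.** The repeated-measures model controls for baseline CRP and for stratum, and "The existence of an interaction between inflammation at baseline and treatment will be assessed". The treatment effect on CRP is to be shown by stratum and overall. The sentence that carries the primary methodology over to other endpoints covers continuous endpoints only.
- **Recruitment and study design.** "In each stratum, participants are randomly allocated in a 1:1 ratio".
- **Objectives.** Superiority is hypothesised for patients with baseline CRP above 3 mg/L. For the others, "no difference between treatments will be observed in individuals with no baseline inflammation".
- **Discussion.** The null expectation in the low-CRP stratum extends to secondary outcomes: "It is hypothesised that primary and secondary outcome measures will not show a statistically significant difference between participants receiving vortioxetine only" and those also given celecoxib in that stratum.
- **Abstract, Methods.** The primary outcome is change in MADRS, "with a primary endpoint of a score reduction by 50% from baseline to six weeks".

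**The concern.** The trial asks whether celecoxib helps patients with raised CRP, and the article expects no effect in the rest. A model with treatment and baseline score alone, fitted to everyone, answers a different question: is there a benefit on average over two strata of equal planned size?

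Two things follow. If the hypothesis is true, the estimate is pulled toward no effect and the test loses power. And because the model does not know the stratum, the same odds ratio would arise if all the benefit lay in the low-CRP stratum, which would contradict the hypothesis.

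This is not detail left to an analysis plan that is not shown. The article states a model, and that model differs from the one stated for MADRS change in the same section.

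**Working it through.** **Plan's own figure.** The article gives no power or response rate for response or remission. Its sample size (50 in each of four groups, power 0.95, alpha 0.05, effect size 0.25) concerns MADRS change. If 0.25 is read as Cohen's f in a 1-df test pooled over four groups, power at 200 is 0.940, close to the stated 0.95. This does not bear directly on the logistic model.

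**Terms side by side.**

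| Outcome | Stratum in model or split | Treatment-by-inflammation term |
|---|---|---|
| MADRS change | yes | yes |
| CRP | split by stratum and total | not applicable to a split |
| Response, remission | no | no |

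**Size of the dilution (illustration).** From the document: 50 per cell, alpha 0.05, and a response odds ratio of 6.59 cited for celecoxib add-on (Medications, Celecoxib). Assumed: a two-sided test, control response p0 of 30%, 40% or 50% in both strata, no effect in the low stratum, no dropout, and baseline score not modelled.

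Let p1 be the celecoxib response in the high stratum. With equal strata, the pooled celecoxib response is (p1 + p0)/2, so the pooled risk difference is (p1 − p0)/2, half the within-stratum difference.

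Hand check at p0 = 0.40 and p1 = 0.65, using power ≈ Φ(Δ/SE − 1.96) with SE = √{[p1(1−p1) + p0(1−p0)]/n}:

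- Within stratum, n = 50 per arm: SE = √[(0.2275 + 0.2400)/50] = 0.0967; 0.25/0.0967 − 1.96 = 0.63; power 0.73.
- Pooled, n = 100 per arm, celecoxib response 0.525: SE = √[(0.2494 + 0.2400)/100] = 0.0700; 0.125/0.0700 − 1.96 = −0.17; power 0.43.

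Exact enumeration of the Wald test on the log odds ratio (treatment only) gives:

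| Benefit in high stratum only | p0 | p1 | OR, stratum | OR, pooled | Power, stratum | Power, pooled |
|---|---|---|---|---|---|---|
| 25 points | 0.30 | 0.550 | 2.85 | 1.72 | 0.736 | 0.447 |
| 25 points | 0.40 | 0.650 | 2.79 | 1.66 | 0.734 | 0.443 |
| 25 points | 0.50 | 0.750 | 3.00 | 1.67 | 0.743 | 0.443 |
| OR 6.59 | 0.30 | 0.739 | 6.59 | 2.52 | 0.996 | 0.905 |
| OR 6.59 | 0.40 | 0.815 | 6.59 | 2.32 | 0.993 | 0.863 |
| OR 6.59 | 0.50 | 0.868 | 6.59 | 2.17 | 0.984 | 0.773 |

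**Reverse case.** By symmetry, a 25-point benefit confined to the low-CRP stratum gives the same pooled result: significant in favour of celecoxib in about 44% of trials, with a high-stratum odds ratio of 1.0.

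**Main effect alone.** In a simulation at 40% v 65%, adding stratum without the interaction left power unchanged at 0.45. The stratum-specific contrast is what recovers it.

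**The case against.** **Pooling is inferred.** The article does not name the population for the logistic model, and treatment plus baseline score is what one would fit separately in each stratum. This stands as a limit. But no sentence restricts the model or asks for results by stratum, whereas the CRP sentence just before it does so explicitly. All participants is therefore the natural reading, not the only one.

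**The primary hypothesis is tested elsewhere.** This also stands. Results analysis makes MADRS change the primary outcome, and that model's stratum and interaction terms allow a contrast in patients with CRP above 3 mg/L. A reader might infer from the Abstract that the trial's primary endpoint is tested in the wrong population. The documents do not support that: only the Abstract treats a 50% reduction as an endpoint, the Discussion uses 50% as an expected size of change for several outcomes, and nowhere is response defined as a 50% reduction.

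**A pooled result would not be misread.** The Discussion ties any recommendation to higher efficacy in inflamed than in non-inflamed participants, so it is speculative that a pooled odds ratio would be taken as support for treating inflamed patients. What stands is that such an odds ratio is uninformative on that comparison.

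**The rates are assumed.** True. With the one response effect the article cites, the loss is milder than under a 25-point benefit.

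**Conclusion.** The point holds for response and remission as secondary, supportive endpoints. The stated model does not match the stratified design, the MADRS-change model beside it, or the stratum-specific expectation that the Discussion extends to secondary outcomes.

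If it is fitted to all participants and the benefit lies only in the high-CRP stratum, the risk difference is halved. In the illustration, power falls from 0.73–0.74 to about 0.44 for a 25-point benefit, and from 0.98–1.00 to about 0.77–0.90 for the cited odds ratio. These figures rest on control rates that are not in the document, equal strata, no dropout and no baseline adjustment; they show the direction and rough size of the loss, not the power of the planned analysis.

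The point does not show that the primary MADRS-change analysis is wrong, nor that the high-stratum response odds ratio should become a second primary test.

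**What to change.** Replace the sentence on dichotomous endpoints with:

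> Response and remission will be analysed by logistic regression with treatment, CRP stratum, treatment-by-stratum interaction and baseline MADRS score. The treatment odds ratio will be reported within each stratum, with the CRP > 3 mg/L contrast as the main one for these endpoints. These analyses are secondary and supportive to the analysis of MADRS change.

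If the Abstract's 50% reduction is meant as a primary endpoint, the Abstract and Results analysis must be reconciled first, because this wording does not provide for a second primary test.

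The cost is one sentence and no new data. The downside is precision: the within-stratum odds ratio uses half the sample. If the effect were in fact equal in both strata (25 points, control 30–50%), power by the same enumeration would be 0.73–0.74 within the stratum against 0.95–0.96 pooled.

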**Fig. 2 Fig2:**
[figure not shown]
Diagram stating the possible dosages of vortioxetine (antidepressant medication) and celecoxib (anti-inflammatory medication) within each group for all the periods of the trial

To promote participant retention, study participants are encouraged to contact the study team if any side effects cause them serious concern between appointments, allowing for the dosage of vortioxetine to be lowered if possible, in the hope of reducing the likelihood of early withdrawal from the study. In the case of early withdrawal from the study, all endpoint scales and blood collection will be conducted immediately for later analysis.

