According to stratified recruitment into the two treatment strata and the random allocation into two treatment groups, participants in both the ‘Depression with inflammation’ and ‘Depression without inflammation’ stratum receive celecoxib 400 mg daily or placebo. The starting dose of vortioxetine in both study strata is vortioxetine 5 mg daily for those receiving celecoxib, due to possible drug–drug interactions, and vortioxetine 10 mg daily for those receiving placebo. Two weeks after commencement of treatment, participants receiving vortioxetine 5 mg daily and 10 mg daily are provided the opportunity to increase to vortioxetine 10 mg or 20 mg daily, respectively, following an assessment by a research clinician (Fig. 2). The decision to increase the dose or to leave it the same is made by the trial psychiatrist after review of the change in depressive symptoms from baseline according to the MADRS and the presence and severity of side effects, rated by a blinded researcher. The dose of vortioxetine is increased only if the side effects experienced are easily manageable and the participants have not achieved recovery (MADRS score < 7). In study participants reporting symptoms consistent with an excessive plasma concentration of vortioxetine, the trial psychiatrist will reduce the dose of vortioxetine without informing the participant or blinded researchers administering scales. After six weeks of treatment, celecoxib and placebo are ceased, but the antidepressant vortioxetine is continued for at least two weeks. After the completion of the RCT phase, study participants are given the opportunity to continue taking vortioxetine into the post-RCT study phase for up to six months. Following an assessment by a research clinician, study participants who had been taking vortioxetine 5 mg or 10 mg daily during the RCT due to celecoxib co-administration are given the opportunity to increase to vortioxetine 10 mg and 20 mg daily, respectively; otherwise vortioxetine is continued in the post-RCT phase at the same dose as for the RCT phase.

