A member of the research team assesses symptoms severity, cognitive function, functional and workplace productivity, and other secondary assessments at baseline visit, fortnightly during the RCT period, and at the three-month and six-month post-RCT visits (see Fig. 1). Participants are asked to report any treatment side effects at each visit. They are also asked to return the vortioxetine packages at each fortnightly visit and receive new ones regardless of whether they have finished a packet or not, so that compliance can be gauged. Similarly, the celecoxib or placebo medication is also returned at the end of six weeks.

An additional checklist and an additional figure have been provided for further details regarding the study of enrolment, interventions and assessments for the current study (Additional file 3 and Fig. 3).

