### Inclusion and exclusion criteria

Participants with MDD are selected according to the following selection criteria: they must be aged 18–75 years; be outpatients in a psychiatric setting with MADRS score ≥ 26 at screening and baseline visits; have at least one prior episode of depression, validated by previous treatment; and the current major depressive episode (MDE) is confirmed by the MINI and has a duration of at least three months. Exclusion criteria are: current alcohol and/or substance use disorder; presence of a co-morbid psychiatric disorder as a focus of clinical concern; primary inflammatory or immune-related disorder; neurodegenerative disorder; history of neurological disorder; past peptic ulcer disease or history of gastrointestinal (GI) bleeding; unstable coronary artery or cardiovascular disease; renal impairment; physical, cognitive, reading, and learning or language impairment. In addition, past hypersensitivity to vortioxetine or to celecoxib and use of concomitant medications able to affect cognitive function or to induce drug–drug interaction are also considered exclusion criteria.

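### LOCF is named as the missing-data and sensitivity analysis, but it assumes no change after withdrawal and does not test the MMRM's missing-at-random assumption

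*Protocol article*

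**What the plan says.** In the Results analysis section of the protocol article, the primary outcome is analysed with a "mixed effects model for repeated measurements (MMRM, all available data), with freely varying mean and covariance structures". Other continuous endpoints use the same method. The section then adds: "Continuous endpoints will also be analysed using observed case (OC) and last observation carried forward (LOCF"), and gives LOCF two tasks: "with LOCF being used to account for missing data and to perform sensitivity analysis". The article names no other missing-data analysis.

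Four other statements bear on the point:

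- **Entry criterion** (Inclusion and exclusion criteria): "MADRS score ≥ 26 at screening and baseline visits".
- **Expected course** (Discussion): the combined treatment "will reduce MADRS score by 50% from baseline to six weeks (end of treatment") in the inflammation stratum.
- **Early withdrawal** (Recruitment and study design): "In the case of early withdrawal from the study, all endpoint scales and blood collection will be conducted immediately for later analysis".
- **Treatment difference between arms** (Study schedule): besides celecoxib or placebo, the vortioxetine starting dose differs, being "vortioxetine 5 mg daily for those receiving celecoxib, due to possible drug–drug interactions, and vortioxetine 10 mg daily for those receiving placebo".

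**The concern.** The MMRM is valid if data are missing at random given what has been observed. A sensitivity analysis should show how far the result moves when that assumption is relaxed by a known amount. LOCF instead assumes that each leaver's score stays where it was at the last visit. In a trial where scores are expected to fall, that value will usually be too high for week 6, and it enters the analysis as though measured, with no allowance for uncertainty.

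The error cancels between arms only if both lose similar numbers of participants at similar times. If they do not, LOCF produces a difference that comes from drop-out and not from treatment. An LOCF result that disagrees with the MMRM would then say nothing about whether missing at random failed, and one that agrees would give little reassurance. At stake is how the robustness analysis can be interpreted, not the primary estimate.

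**Working it through.** The article gives no drop-out rate, SD or visit-by-visit trajectory, so there is no figure of its own to reproduce. What follows is illustrative.

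**From the article.** Visits are fortnightly, so a value carried to week 6 comes from baseline, week 2, week 4 or a withdrawal visit. A 50% fall from the minimum entry score of 26 is 0.50 × 26 = 13 points, so substantial change is expected in at least the group for which the 50% is stated.

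**Assumed.** Mean MADRS 32, 26, 21, 18 at weeks 0, 2, 4, 6 in both arms (no true treatment difference), SD 9, drop-out 10% in one arm and 20% in the other.

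**Formula.** With equal true trajectories and leavers typical of their arm:

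spurious difference = (difference in drop-out proportion) × (mean fall still to come after the last visit).

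**Results.**

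- Fall still to come after week 2: 26 − 18 = 8 points. After week 4: 21 − 18 = 3 points.
- Leavers split equally between the two times: 0.10 × (8 + 3)/2 = 0.55 points; 0.55/9 = 0.06 SD.
- All leave after week 2: 0.10 × 8 = 0.80 points; 0.80/9 = 0.09 SD.
- All leave after week 4: 0.10 × 3 = 0.30 points; 0.30/9 = 0.03 SD.
- Equal drop-out: 0 × 8 = 0.
- Imbalance reversed: same size, opposite sign.

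**Other shapes and effects.**

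- With a linear 16-point fall, two thirds remains after week 2: 0.10 × 10.67 = 1.07 points (0.12 SD). At 10% v 30% drop-out this becomes 0.20 × 10.67 = 2.13 points (0.24 SD).
- With a true 3-point difference that builds linearly (1 point by week 2) and equal drop-out *d* after week 2, LOCF estimates 3 − *d* × (3 − 1): 2.8, 2.6 and 2.4 points for *d* = 10%, 20% and 30%.

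**Simulation under missing at random.** There were 4,000 trials with 100 per arm, no true effect, a linear 16-point fall, SD 9 and correlations of 0.70 between adjacent visits and 0.55 between weeks 2 and 6. Drop-out after week 2 was likelier with a higher week-2 score, averaging about 10% and 20% in the two arms. A regression estimator valid under missing at random stood in for the MMRM.

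| Method | Mean difference at week 6 (true value 0) |
|---|---|
| Missing-at-random estimator | 0.01 points |
| Observed case | 0.39 points, favouring the arm with more drop-out |
| LOCF | 1.26 points, favouring the arm with less drop-out |

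The LOCF test rejected in 12.7% of trials against a nominal 5%. So LOCF can contradict a valid analysis when missing at random is true.

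**The case against.** The strongest reply is that LOCF is only supplementary. The MMRM carries the primary inference, and it is not wholly clear that the continuous endpoints sent to LOCF include MADRS change. LOCF also does assume something other than missing at random, so it is a departure of a kind. The first part stands and limits the consequence. The second is true but does not help: the departure is fixed by whatever the last score happened to be and cannot be scaled to see when the conclusion would change.

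Several stronger readings are tempting, and the article does not support them:

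- **A reader might infer that the trial has no valid check on informative drop-out.** A condensed article cannot show that, because a separate analysis plan may name further analyses. What can be criticised is the role that the article itself gives to LOCF.
- **A reader might infer that withdrawal assessments enter as week-6 values.** The article says only that they are done at once for later analysis, not at which time point they are used.
- **A reader might infer that MADRS is expected to fall steadily in every group.** The Discussion states 50% for one group. Some fall elsewhere is implied, but no shape is given.
- **A reader might take the differing vortioxetine doses as evidence of unequal drop-out.** The article presents the lower dose as an offset for a drug interaction and assumes comparable plasma concentrations. Unequal drop-out remains possible, since one arm also takes celecoxib and the article links side effects to withdrawal, but neither its size nor its direction is known.
- **A reader might set 0.06 to 0.09 SD against the planned effect size of 0.25 and call it a quarter to a third.** That takes 0.25 as a between-arm standardised difference, which would need 2 × (1.96 + 1.645)²/0.25² ≈ 416 per arm, far from 200 in total. Read as Cohen's f, 0.25 corresponds to d = 0.5. A comparison of 100 v 100 then has about 94% power, and the share is 0.06/0.5 to 0.09/0.5, or about 12% to 18%.

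**Conclusion.** The point holds for the robustness analysis. LOCF is a poor choice for the role the article assigns to it: its no-change assumption conflicts with the improvement the protocol expects, and neither it nor the observed-case analysis tests the assumption on which the MMRM depends.

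Under the assumed trajectory, SD 9 and 10% v 20% drop-out, the spurious difference is 0.55 to 0.80 points (0.06 to 0.09 SD). It is smaller if all leave after week 4, larger under a linear fall or a wider imbalance, and zero with equal drop-out and no true effect. Its direction depends on which arm loses more participants, so LOCF cannot be relied on as conservative.

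The primary MMRM estimate is not affected. If MADRS change is not among the continuous endpoints meant, the fault applies to the secondary ones.

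**What to change.** - Keep the MMRM on all available data as the primary analysis.
- In the sensitivity role, replace LOCF with multiple imputation under delta adjustment, worsening the imputed scores by increasing amounts, separately by arm, until the conclusion changes (tipping point). Reference-based imputation, with celecoxib-arm leavers imputed from the placebo arm, can be used in addition or instead.
- If LOCF is kept for comparison with older trials, label it descriptive and remove the statement that it accounts for missing data.
- State whether the primary MADRS outcome is covered by these analyses.
- State that assessments made at early withdrawal are analysed at the time they were made and not as week 6.

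The cost is a change of wording, agreement in advance on the range of deltas, and modest extra programming. Treatment and data collection do not change.
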